# Positive behavior support in school – a quasi-experimental mixed methods study and a randomized controlled trial

**DOI:** 10.1186/s40359-024-02021-z

**Published:** 2024-10-01

**Keywords:** Quasi-experimental design, School-wide positive behavioral interventions and supports, SW-PBIS, School Climate, Intervention

## Abstract

**Background:**

While positive school climate is important for students’ well-being and mental health, school personnel may experience challenges in creating a nurturing school climate. School-Wide Positive Behavioral Interventions and Supports (SW-PBIS) has shown positive effects on school climate and children’s prosocial behaviors, but fewer studies have been conducted in a European context.

**Aim:**

This project aims to investigate the effectiveness of SW-PBIS program for students’ social-emotional skills and academic achievement as well as teachers’ and students’ perceptions of classroom learning environment. Furthermore, the study intends to evaluate how school-level factors mediate or moderate the effects of the intervention. In addition, the study includes a qualitative evaluation of the dynamic interaction processes that occur during program implementation in local school contexts.

**Methods:**

Data on school- and individual-level measures are collected in intervention and control schools. With regard to challenges in retaining control groups over extended time periods, two waves of recruitment are used. In the first wave, an active control group is used and data are collected during three time points. In the second wave, a wait-list control group will be used and data will be collected during two time points during one school year. Hierarchical regression analyses will be conducted to explore the effects of SW-PBIS on the outcomes of the study. An ethno-methodological approach will be applied to provide a detailed examination of the social interactional and meaning-making practices of different school implementation teams, and the negotiation of normative expectations and rules of conduct in peer-teacher-student interactions in different classrooms.

**Discussion:**

The study is expected to contribute to knowledge on the effects of the SW-PBIS program and how these effects may be mediated or moderated by school-level factors. Combining quantitative and qualitative methods to explore the significance of school contexts in the implementation of the SW-PBIS program constitutes the strength of the study. The challenge in the study is the extended period of implementation of SW-PBIS, which entails difficulties in retaining a control group over the required time period. Therefore, two waves of recruitment are used, encompassing different procedures of allocation to intervention or control group.

**Trial registration:**

ClinicalTrials.gov Identifier: NCT06270914 on the 22nd of February, 2024 (retrospectively registered).

**Supplementary Information:**

The online version contains supplementary material available at 10.1186/s40359-024-02021-z.

## Background

Creating a nurturing school and classroom climate is essential for students’ mental health, well-being and school achievement [1]. Poor classroom and school climate has a negative impact on students’ behaviors [e.g., 2, 3], while positive relationships with teachers, characterized by warmth and emotional support, may alter the course of negative development for children at risk [4, 5]. Furthermore, children who do not fully master the skills necessary to focus on school tasks and to get along with peers, may exhibit behaviors perceived as challenging. Schools’ response to these behaviors often involves disciplinary measures, leading to less instructional time necessary to achieve academically [e.g., 6]. In combination with a lack of nurturing relationships at school or at home this in turn puts this group of children at a heightened risk for school dropout, poor mental health and in the long run unemployment and for some even contacts with criminal justice [e.g., 7]. Thus, addressing school climate is urgent to prevent problem behaviors and promote positive school climate and mental health outcomes for children and youth.

The study focuses on the program School-Wide Positive Behavioral Interventions and Supports (SW-PBIS), which is a systems-level approach to address behavior problems and promote social behaviors by targeting school and classroom organization [8]. The program is grounded in multiple theories, including applied behavior analysis [9], social learning theory [10], coercion theory [11] and ecological theory [12]. The strength of the program is its collaborative nature, as it focuses on whole school prevention of behavior problems.

The evidence base of the SW-PBIS is well established. According to a recent review [13], the program resulted in reduction of behavior problems and increase in prosocial behaviors; as well as improvements in teachers’ and students’ perceptions of school climate. While research base for SW-PBIS in North American context is extensive, fewer studies have been published in Europe [14–16]. These studies have shown promising results concerning student and teacher behaviors, classroom climate, and peer relations. A study of SW-PBIS in Swedish schools reported no positive effects of the program [17]. The authors reported challenges in implementation as possible explanations for null results. Thus, it is yet left to be found out if, when and how SW-PBIS program is effective in Swedish school settings.

Previous studies also raise questions of the conditions under which the SW-PBIS program is effective, and for whom. First, at the individual level, the SW-PBIS program demonstrates higher effects for students who are at risk for behavior problems at baseline [14, 18]. Second, schools who implement the SW-PBIS with fidelity also appear to rip benefits of the program to a higher degree [13, 19]. School contextual factors (e.g., school size, location, team functioning) and teacher level factors (e.g., grade taught, perceived classroom climate) are associated with the variability in fidelity of implementation of SW-PBIS [20]. In addition, teacher self-efficacy has been outlined as one of the positive outcomes of SW-PBIS [21], but no study explored whether changes in teacher self- efficacy are related to changes in student behaviors. Thus, a consideration of multiple factors, would contribute to our understanding of how, when and for whom the SW-PBIS program is effective.

Social issues related to power asymmetries between teachers and students and ethical dilemmas are also crucial dimensions in social processes of implementation. These issues are something that further strengthens the need for a more detailed inquiry into how the core components in the SW-PBIS programs, as rules and behavioral expectations, are handled and negotiated in student-teacher interactions in the classroom. The complexity of teachers’ everyday classroom encounters has been brought about in studies of teacher-student interaction and co-construction of classroom norms from the perspectives of teachers and students [22, 23]. It is also important to focuse on teachers’ normative expectations in managing students’ challenging behavior and the emotionally charged nature of issues in classroom management [24]. The proposed project makes an important contribution to the field by an in-depth exploration of the processes that emerge and take form as teachers and students participate in the implementation of the SW-PBIS program.

## Aim

The aim of the project is twofold. Firstly, the aim is to evaluate the effectiveness of SWPBIS program for students’ social-emotional skills and academic achievement as well teachers’ and students’ perceptions of learning environment and to explore how school-level factors may moderate or mediate the effect of SWPBIS on the outcomes. Secondly, the aim is to get a deeper understanding of the social processes and local meanings that emerge and take form among the students, teachers and other school professionals as they participate in the SW-PBIS program. The aims are specified in four research questions.

What are the effects of SW-PBIS program on students’ social-emotional skills and academic achievement as well teachers’ and students’ perceptions of learning environment?To what extent do school level factors mediate and moderate the effects of the SW-PBIS program on the study outcomes over time?How are the central contents of the SW-PBIS program made sense of and negotiated in school teams and classrooms at two schools during the course of program implementation?How do specific instances of student-teacher interaction lead to changes in students’ behavior and responses to the SW-PBIS program, and what forms of ethical dilemmas evolve in the management of behavior problems in classrooms?

## Methods: participants, interventions and outcomes

This study includes two waves of participant recruitment with two designs: quasi-experimental non-randomized design (wave 1) and cluster-randomized design (wave 2). The intervention study has been approved by the Swedish Ethical Review Authority (2022-03482-01), and registered as a clinical trial at www.clinicalTrials.gov (identifier NCT06270914). The choice of two waves of recruitment is motivated by the challenge to retain a control group over two years, as previous studies have implemented SW-PBIS for three to four years [16, 18]. Therefore, two waves of recruitment are used. In the first wave of recruitment, intervention and active control group are used and outcomes will be measured at three time points. In addition to quantitative data, qualitative observations and interviews are conducted to get a deeper understanding of the process of implementation of SW-PBIS. In the second wave of data recruitment, intervention and wait-list control group are used and outcomes will be measured at two time points (pre- and post). In Fig. 1, recruitment and data collection for both waves of data collection are described.

**Fig. 1 Fig1:**
[figure not shown]
Two waves of data collection in the project (produced through the web-based application draw.io at www.diagrams.net (accessed on 30 May 2024)

### Participants

The study will be conducted in compulsory schools and include classes from grade one to grade nine. Inclusion criteria for the intervention and control groups are: (a) compulsory school, grades 1–9; (b) the school have not been previously enrolled in an SW-PBIS program by other providers (b) principal, teachers, students and their parents consent to participate in the study. Each of the two waves of recruitment in the study will include 80 schools. According to estimations with the software Optimal Design [25], 62 schools are required, based on an effect size of 0.25 and a power of 80%, with an expected amount of 12 classes per school, 20 students per class and an intraclass correlation (ICC) of 0.10 at school level and 0.05 at classroom level [26]. To account for 20% attrition, 80 schools are needed. Based on previous studies of SW-PBIS in the European context [14, 32], we expect Cohen’s d effect size of 0.20 to measure an important difference between the intervention and control group.

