### Recruitment

Information about the study will be distributed by e-mail to all compulsory schools in Sweden. The e-mail lists will be retrieved from Swedish National Agency for Education. In addition, information about the study will be distributed at conferences and via regional principal and teacher networks. School principals and teachers will be invited to online meetings at which detailed information about the study will be presented and detailed information on participation in the study will be provided. Upon enrollment in the project, the information and invitation to participate in the study is distributed to students’ guardians. In addition to Swedish language, information about the study will be presented in ten frequent languages in Sweden (Arabic, Spanish, English, Somali, Serbo-Kroatian, Polish, Kurdish, Finnish, Farsi, and Urdu). Students in grade 9 will also be asked for informed consent, upon consent from both guardians.

In the first wave of recruitment, the decision to allocate participants to intervention or control group will be based on the school principals’ choice of intervention. The schools, catering for students in grades 4–9, which have expressed interest in the intervention, will be stratified in three groups, based on size, parent educational level, proportion of students with migrant background and students’ average achievement rates. This information is publicly available from SALSA database of the National Agency for Education. After stratification, schools within each stratum will be assigned to intervention group. The same procedure will be conducted in the recruitment of control groups. In the second wave of recruitment, the participants from schools grades 1–9 will be recruited the study, and then randomly allocated to either intervention or control group.

According to estimations with the software Optimal Design (OD; Spybrook et al., 2011), 62 schools are required, based on an effect size of 0.25 and a power of 80% with an expected amount of 12 classes per school, 20 students per class and an intraclass correlation (ICC) of 0.10 at school level and 0.05 at classroom level (Hedges & Hedberg, 2007). To account for 20% attrition, 74 schools are needed (approximately 17 280 students). Therefore, in each wave of data collection, a minimum of 74 schools will be recruited.

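### The 62 schools for 80% power at d = 0.25 are not reproduced under conventional settings (57 schools; 62 give about 84%), and the attrition, student and effect-size figures built on 62 do not agree

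*Protocol article*

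**What the plan says.** The Participants section of the protocol article reports a calculation made with the Optimal Design software: "62 schools are required, based on an effect size of 0.25 and a power of 80" per cent. The cluster sizes are 12 classes in each school and 20 students in each class. For clustering, the section assumes "an intraclass correlation (ICC) of 0.10 at school level and 0.05 at classroom level". The Recruitment section repeats the same inputs and the same 62.

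The two sections then part. Participants says "To account for 20% attrition, 80 schools are needed" and plans 80 schools in each wave. Recruitment says "To account for 20% attrition, 74 schools are needed", equates this with approximately 17 280 students, and sets 74 as the minimum per wave.

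Participants also names a second effect size. Citing earlier European studies, it expects a Cohen's d "effect size of 0.20 to measure an important difference between the intervention and control group". No power is given for that value.

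Neither section states alpha, whether the test is one- or two-sided, the allocation ratio, or the SD that standardises the effect. For wave 2, Recruitment says only that schools are recruited "and then randomly allocated to either intervention or control group".

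**The concern.** The article prints enough of a three-level cluster calculation for a reader to repeat it, and the usual calculation does not return 62. That leaves two possibilities: the size and power do not belong together, or 62 rests on a setting or value that the article does not show.

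The number matters because both waves are sized from it. The attrition-adjusted totals start from 62, and those totals disagree with each other. The margin that 62 appears to give at d = 0.25 also draws attention away from d = 0.20, the effect the plan says it expects, for which no power is reported.

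**Working it through.** **Inputs from the article:** d = 0.25; power 80%; J = 12 classes per school; n = 20 students per class; ICC 0.10 (school) and 0.05 (class); 20% attrition; expected d = 0.20.

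**Assumptions, not in the article:** two-sided 5%; 1:1 allocation; effect standardised by the total SD; noncentral t with K−2 df, where K is the total number of schools.

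**Step 1. Variance of the treatment effect, treatment at school level**

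Var = (4/K) × [ICC_school + ICC_class/J + (1 − ICC_school − ICC_class)/(J·n)]

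= (4/K) × [0.10 + 0.05/12 + 0.85/240] = (4/K) × 0.10771 = 0.4308/K

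**Step 2. Attempt to reproduce 62.** The noncentrality is d/√(0.4308/K). At K = 62 and d = 0.25 it is 3.00.

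| Schools (K) | Power at d = 0.25 | Power at d = 0.20 |
|---|---|---|
| 56 | 0.799 | 0.610 |
| 57 | 0.8065 | 0.618 |
| 58 | 0.813 | 0.626 |
| 59 | 0.820 | 0.633 |
| 62 | 0.839 | 0.656 |
| 64 | 0.851 | 0.670 |
| 80 | 0.920 | 0.768 |
| 87 | 0.940 | 0.802 |

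The smallest K with 80% power at 0.25 is 57 (58 if the arms must be equal). The stated 62 is not reproduced; it gives 83.9%.

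**Step 3. Settings that miss or reach 62**

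| Change from Step 2 | Result at d = 0.25 |
|---|---|
| One-sided 5% | 45 schools |
| Two-sided 2.5% | 69 schools |
| Two-level model, 240 per school, ICC 0.10 | 55 schools |
| Two-level model, 240 per school, ICC 0.15 | 80 schools |
| Effect standardised by the within-school SD (bracket 0.10771/0.9 = 0.1197) | 79.9% at 62 |
| Allocation about 35:65 | 80.4% at 62 |
| 5 classes per school instead of 12 | 62 schools |
| School ICC 0.11 instead of 0.10 | 62 schools |

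The within-school SD and the 35:65 split fill gaps that the article leaves open. The last two rows contradict values that it prints.

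**Step 4. Attrition**

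- 62/(1 − 0.20) = 77.5, so 78 schools. The 80 in Participants covers this with a small margin: 80 × 0.80 = 64.
- 62 × 1.2 = 74.4, which accounts for the 74 in Recruitment. But 74 × 0.80 = 59.2, so about 59 remain, fewer than the 62 stated as required.

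**Step 5. Student total**

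- 12 × 20 = 240 students per school.
- 74 × 240 = 17 760.
- 17 280/240 = 72 schools exactly.
- The gap is 480 students, and 480/17 280 = 2.8%.

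**Step 6. The expected effect of 0.20.** From the table, power is 65.6% with 62 schools, 63.3% with the 59 left from 74, and 67.0% with the 64 left from 80. Under the same assumptions 80% power would need 87 analysed schools.

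**The case against.** A reader might infer that the article gives every input, so that 62 is a proven error and a printed ICC or class count must be wrong. The documents do not support that. Alpha, sidedness, allocation and the standardising SD are absent, and an article may leave such settings to a fuller document. A within-school SD or a split near 35:65 brings 62 to 80% without contradicting anything printed. Unequal arms are not far-fetched in wave 1, where principals choose the intervention, and no ratio is fixed for either wave. This part of the objection stands. What can be said is that 62 is not reproduced under conventional settings, not that it is wrong.

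The discrepancy is also in the safe direction at 0.25. Under the Step 2 model even 59 schools give 82%, and 64 give 85%. That stands too: the trial is not underpowered at 0.25 on these inputs.

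The student total is worded as approximate, is off by 2.8%, and drives no analysis. Nor can it be traced to the 62, since 72 follows from neither 62/0.8 nor 62 × 1.2. It is a small inconsistency. One could note that 57/0.8 = 71.25 rounds up to 72 and infer an earlier calculation with 57 schools, but that is only suggestive.

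Finally, the shortfall at 0.20 exists whether the base number is 57 or 62, so correcting 62 would not repair it. That is right, and it is why power at 0.20 has to be reported in its own right. None of these objections removes the conflict between 80 and 74 for the same attrition, or the fact that 74 leave fewer schools than the plan says it needs.

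**Conclusion.** The point holds in a limited form. With two-sided 5%, 1:1 allocation, a total-SD effect size and K−2 df, the printed inputs give 57 schools (58 balanced), and 62 give about 84% rather than 80%. The stated number is 5 schools above the recomputed one (5/57, about 9%) and the power differs by about 4 points, both conservative at 0.25. Because the four settings are unstated, whether 62 is a slip or reflects an unreported choice cannot be settled from the article.

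Two consequences do not depend on how 62 arose. The same 20% attrition is turned into 80 schools in one section and 74 in the other, and the lower figure leaves about 59, below the stated requirement. And the stated 80% belongs to d = 0.25, while the plan expects 0.20. At that value power is about 63% to 67% for the schools left after attrition; this range rests on the Step 2 assumptions. The mismatch between 17 280 students and 74 schools is minor.

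The sample-size statement should be corrected, since it governs both waves and the change is cheap.

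**What to change.** 1. Re-run the calculation and state alpha, sidedness, allocation ratio and the SD that standardises the effect.
2. If 62 came from a setting or value not shown, print it or correct the input. Otherwise restate the result as 57 schools (58 balanced) for 80% power at 0.25, with about 84% for 62.
3. Use one attrition-adjusted number of schools in Participants and Recruitment, obtained by dividing by 0.80. If 62 is kept, that is at least 78.
4. Report power at d = 0.20 for the schools expected after attrition.
5. Restate the student total as the final number of schools × 240.

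The cost is wording and one repeat calculation. No additional schools are asked for. The price is that the article will show a less favourable power at the effect it expects.

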### Recruitment

Information about the study will be distributed by e-mail to all compulsory schools in Sweden. The e-mail lists will be retrieved from Swedish National Agency for Education. In addition, information about the study will be distributed at conferences and via regional principal and teacher networks. School principals and teachers will be invited to online meetings at which detailed information about the study will be presented and detailed information on participation in the study will be provided. Upon enrollment in the project, the information and invitation to participate in the study is distributed to students’ guardians. In addition to Swedish language, information about the study will be presented in ten frequent languages in Sweden (Arabic, Spanish, English, Somali, Serbo-Kroatian, Polish, Kurdish, Finnish, Farsi, and Urdu). Students in grade 9 will also be asked for informed consent, upon consent from both guardians.

In the first wave of recruitment, the decision to allocate participants to intervention or control group will be based on the school principals’ choice of intervention. The schools, catering for students in grades 4–9, which have expressed interest in the intervention, will be stratified in three groups, based on size, parent educational level, proportion of students with migrant background and students’ average achievement rates. This information is publicly available from SALSA database of the National Agency for Education. After stratification, schools within each stratum will be assigned to intervention group. The same procedure will be conducted in the recruitment of control groups. In the second wave of recruitment, the participants from schools grades 1–9 will be recruited the study, and then randomly allocated to either intervention or control group.

According to estimations with the software Optimal Design (OD; Spybrook et al., 2011), 62 schools are required, based on an effect size of 0.25 and a power of 80% with an expected amount of 12 classes per school, 20 students per class and an intraclass correlation (ICC) of 0.10 at school level and 0.05 at classroom level (Hedges & Hedberg, 2007). To account for 20% attrition, 74 schools are needed (approximately 17 280 students). Therefore, in each wave of data collection, a minimum of 74 schools will be recruited.

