### Data analyses

Hierarchical regression analyses with a three-level structure [38] will be conducted to explore the effects of the SW-PBIS on study outcomes. Hierarchical regression analyses allow to account for the nested structure of the data, in which teachers’ and students’ responses are nested within schools and grade levels. The outcomes at school and individual level will be studied as a function of time (three time points for wave 1 and two time points for wave 2) and group belonging (intervention or control group). To take into account the nestedness of the data, three-level random effect model will be used, varying by school, grade and the individuals’ identification codes. Furthermore, the possible mediators (quality of implementation) and moderators (school characteristics, school-level variables) of the SW-PBIS intervention will be analyzed. Missing data will be handled by imputation, provided that the assumption of data missing completely at random is met.

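### Wave 2 randomisation and its main effect model are not tied to the public school variables that wave 1 stratifies on, which gives up some balance and precision but causes no bias

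*Protocol article*

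**What the plan says.** The Protocol article describes a "quasi-experimental non-randomized design (wave 1) and cluster-randomized design (wave 2").

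Under Recruitment, the wave 1 schools "will be stratified in three groups, based on size, parent educational level, proportion of students with migrant background and students’ average achievement rates". The article adds: "This information is publicly available from SALSA database of the National Agency for Education". In that wave the arm follows the principal's choice. The next sentences turn to wave 2, where participants are "recruited the study, and then randomly allocated to either intervention or control group". No stratification, matching or other restriction is named for wave 2, and the allocation is not called simple or unrestricted either.

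Under Data analyses, outcomes are modelled as a function of time and "group belonging (intervention or control group"), with random effects for school, grade and individual. The same paragraph lists school characteristics and school-level variables as moderators to be analysed. It does not name them as adjustment covariates for the main effect. Wave 2 outcomes are measured before and after the intervention.

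**The concern.** Stratification is described for the wave in which it cannot balance the arms, because principals choose the arm. It is not described for the wave in which it could. Wave 2 has one randomisation of roughly 74 to 80 schools, and the treatment contrast is made between schools, so school-level variation limits precision.

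The article itself gives reasons to care about school type. The Background links school size and location to implementation fidelity, and fidelity to benefit. The Discussion expects effects to vary with school-level factors. At stake are the precision of the wave 2 effect, the credibility of the comparison if the arms differ visibly in school type, and the support for the planned moderator analyses.

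**Working it through.** **Inputs from the Protocol article (Participants).** The sample size statement reads "62 schools are required, based on an effect size of 0.25 and a power of 80" (per cent). Each school is taken to have 12 classes, and each class 20 students. The ICCs are 0.10 (school) and 0.05 (classroom). On the expected effect, the article says "we expect Cohen’s d effect size of 0.20 to measure an important difference between the intervention and control group". Attrition of 20% from 80 schools leaves 64. **Assumed, not in the article:** two-sided alpha 0.05 and 1:1 allocation.

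**1. The plan's own figure.** For a single post-measurement without covariates, Var(d) = 4v/K, with

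v = 0.10 + 0.05/12 + 0.85/240 = 0.1000 + 0.0042 + 0.0035 = 0.1077.

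At d = 0.25 and 80% power this gives K = 54.1 (normal approximation), or 57 schools with the t distribution (58 if even), against 62 stated. Power at 62 is 83.9%. The stated figure is not reproduced exactly. It is mildly conservative and leaves no sign of a gain from covariates or strata. The school term is 0.1000/0.1077 = 93% of v, but this share applies to a post-only comparison.

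**2. Chance imbalance.** Under unrestricted 1:1 allocation, the SD of the between-arm difference in a standardised school variable is 2/√K.

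| Schools | SD | P(gap > 0.25 SD) | P(gap > 0.5 SD) |
|---|---|---|---|
| 80 | 0.224 | 26% | 2.5% |
| 74 | 0.232 | 28% | 3.2% |
| 62 | 0.254 | 32% | 4.9% |

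**3. Main effects in a time-by-group model.** With complete data the effect is the difference between arms in post minus pre. A school variable that is constant over time and enters as a main effect cancels from that difference. Simulated two-time-point data (62 schools, half of the school variance explained by the covariate) agree: the estimate was the same with and without the covariate, and in one example the standard error was 0.0506 both times.

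**4. Gain after baseline adjustment.** Let r be the school-level pre-post correlation. Let R2 be the share of school variance explained by the four variables, taken as equal at both time points. Both are assumed. Adjusting for the pre-measure leaves school variance 0.10(1 − r²). The variables then explain a further share of that remainder,

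f = R2(1 − r) / [(1 + r)(1 − R2)].

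The variance per school becomes 0.10(1 − r²)(1 − f) + 0.0077, with the class and student terms left unchanged. Power is at d = 0.20 with 64 schools, using noncentral t with one df for the pre-measure and four for the variables.

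| r | R2 | f | v without → with | SE reduction | Power without → with |
|---|---|---|---|---|---|
| 0.5 | 0.2 | 0.083 | 0.0827 → 0.0765 | 3.9% | 78% → 81% |
| 0.5 | 0.3 | 0.143 | 0.0827 → 0.0720 | 6.7% | 78% → 83% |
| 0.7 | 0.2 | 0.044 | 0.0587 → 0.0565 | 1.9% | 90% → 91% |
| 0.7 | 0.3 | 0.076 | 0.0587 → 0.0549 | 3.3% | 90% → 92% |
| 0.7 | 0.5 | 0.176 | 0.0587 → 0.0497 | 8.0% | 90% → 94% |

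The gain is larger if the variables also predict change. If they explain 10 to 30% of the remaining school variance at r = 0.7, power goes from about 90% to between 92.5% and 96.5%.

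**The case against.** The strongest reply is that this reads silence in a condensed article as a design. Stratification and sequence generation are often left to the full protocol, and adjustment covariates to the analysis plan. That stands against two readings a reader might infer. The article does not say that wave 2 uses simple or coin-flip randomisation, so the 22% chance of a split worse than 45:35, which holds only for independent coin flips, has no basis in the text. Nor does it say the school variables are left out of the analysis, since they are named as moderators. What remains is that Recruitment sets the two procedures side by side, and gives strata to the wave that is not randomised and none to the wave that is.

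A second reply concerns size. For a post-only comparison of 62 schools at d = 0.20, power would rise from 66% to 74%, 79% or 90% if the variables explained 20%, 30% or 50% of school variance. Those R2 values are assumed, and wave 2 has a pre-measure that may absorb much of the same variance, so the figures do not describe the planned analysis. National-test achievement, perhaps the outcome closest to these variables, is collected only in wave 1. This reply stands and limits the point to a modest gain. It does not remove it: if the pre-post model acts as a change score and r = 0.5, the school-level variance 2(1 − r) × 0.10 is again 0.10, so the pre-measure brings no gain at school level.

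A third reply is that chance imbalance is ordinary and already reflected in the standard error. That is correct for validity. It does not answer the loss of precision.

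**Conclusion.** The point holds as an inexpensive improvement to the stated wave 2 procedure. It is not an error that threatens the trial. Its firm part is the text: four public school variables are used to stratify wave 1, but are tied neither to wave 2 allocation nor to the main effect model as adjustment covariates. With 80 schools and unrestricted 1:1 allocation, the chance of a gap above 0.25 SD is about 26% per variable. A figure of 71% for at least one of the four would require the variables to be independent, which the article does not support.

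A reader might infer that the wave 2 comparison is biased. It is not: randomisation protects it, and the cost is in precision and face validity. The size of the precision gain cannot be derived from the article. Under the assumptions in step 4 it is a 2 to 7% smaller standard error for R2 of 0.2 to 0.3, and 8% for R2 of 0.5 with r = 0.7.

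**What to change.** State whether wave 2 allocation is restricted, and how.

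- **If allocation is still open:** randomise schools 1:1 within the strata defined for wave 1. Wave 2 also takes in grades 1–3, so confirm first that all four variables are on record for every wave 2 school.
- **If allocation is done:** keep it.
- **In both cases:** prespecify the strata or the four variables in the wave 2 effect model, in a form that can affect the contrast. This means either a baseline-adjusted (ANCOVA-type) model of the post-measure with these covariates, or covariate-by-time terms in the time-by-group model. The moderator analyses remain separate.

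Any power gain that is quoted should state the assumed R2 and pre-post correlation. The cost is one line in the allocation procedure, one in the analysis and about four school-level degrees of freedom. No new data collection is needed, because the article describes the variables as public.

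### The same 62 schools and 20% attrition give 80 schools in one section and 74 in another; 74 leaves about 59, below the 62 required

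*Protocol article*

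**What the plan says.** Two sections of the protocol article's Methods report the same calculation. The inputs are "62 schools are required, based on an effect size of 0.25 and a power of 80" per cent, "12 classes per school, 20 students per class", and an "intraclass correlation (ICC) of 0.10 at school level and 0.05 at classroom level". Both sections allow for 20% attrition.

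- **Participants:** "To account for 20% attrition, 80 schools are needed". The section also states: "Each of the two waves of recruitment in the study will include 80 schools".
- **Recruitment:** "To account for 20% attrition, 74 schools are needed", followed in brackets by "approximately 17 280 students". It then concludes that "in each wave of data collection, a minimum of 74 schools will be recruited".

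Nothing in the article explains the difference between the two results.

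**The concern.** One set of inputs cannot need both 80 and 74 schools. If the lower number is wrong, the stated recruitment minimum does not deliver the number of schools the plan says it requires once the planned losses occur.

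The school count deserves care here. Schools are the clusters, so their number largely determines power. The article also names retention of control schools as a main challenge and gives it as the reason for using two waves. As written, a wave that stops at 74 satisfies the Recruitment section and fails the Participants section, so a reader cannot tell whether recruitment met its target.

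**Working it through.** **Inputs (Participants and Recruitment sections, identical in both):** 62 schools required; 20% attrition; 12 classes × 20 students = 240 students per school; effect size 0.25; ICC 0.10 for schools and 0.05 for classrooms.

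**1. Where the two school counts come from.** To keep n schools after losing a fraction d, recruit n/(1 − d).

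- 62/(1 − 0.20) = 77.5, so 78 schools.
- The 80 in Participants is consistent with this, with a margin of two schools.
- The 74 in Recruitment is not. It matches n × (1 + d): 62 × 1.20 = 74.4, rounded down. The article gives no formula, so this origin is an inference, but it is a common slip and fits the number.

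**2. Schools left after 20% attrition.**

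| Recruited | × 0.8 | Against 62 |
|---|---|---|
| 74 | 59.2 | about 3 short |
| 78 | 62.4 | met |
| 80 | 64.0 | met |

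Starting from 74, the loss that still leaves 62 schools is 1 − 62/74 = 16.2%.

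**3. Student total, at 240 per school.**

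| Schools | Students | Minus 17,280 |
|---|---|---|
| 72 | 17,280 | 0 |
| 74 | 17,760 | 480 |
| 78 | 18,720 | 1,440 |
| 80 | 19,200 | 1,920 |

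The printed total corresponds to exactly 72 schools, a number that appears nowhere in the article.

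**4. What the shortfall costs in power.** The article gives neither alpha nor allocation ratio. I assumed two-sided alpha 0.05 and 1:1 allocation of J schools, with total variance 1.

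- Variance of a school mean: 0.10 + 0.05/12 + 0.85/240 = 0.1077.
- Standard error of the difference: √(4 × 0.1077/J).
- Power from the noncentral t distribution with J − 2 degrees of freedom and noncentrality 0.25/SE.

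| Schools analysed | Power at 0.25 |
|---|---|
| 59 (74 less 20%) | 82.0% |
| 62 (stated requirement) | 83.9% |
| 64 (80 less 20%) | 85.1% |

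Under these assumptions 80% power is reached with 57 schools, so the plan's 62 is not reproduced exactly and looks somewhat conservative.

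**The case against.** The strongest reply is that the discrepancy does little harm. With 59 schools, power at 0.25 is still about 82%, above the 80% sought, and the loss against 62 is about 2 percentage points. That stands, and it limits the weight of the point. It depends on an alpha and an allocation ratio that the article does not state, and in wave 1 allocation follows the principals' choice, so equal groups are not assured.

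A second reply is that the two recruitment commitments are compatible: a wave of 80 schools also satisfies a floor of 74. That is true of those two sentences. It does not reconcile the two statements of how many schools are needed for the same attrition, and a floor should itself meet the requirement it is derived from.

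A third reply is that the student total is described as approximate, and that 480 out of 17,760 is a gap of only 2.7%. This is fair. The total is the weakest part of the point and has no bearing on power. Even so, it equals 72 × 240 exactly, so it looks like a leftover from another school count and not a rounding.

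The article also mentions an expected effect of 0.20, for which power would be lower at any of these school counts. That is a separate matter and adds nothing to the case here.

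**Conclusion.** The point holds. From the plan's own 62 schools and 20% attrition, the number to recruit is at least 78. The 80 in Participants is adequate. The 74 in Recruitment is four schools too few and leaves about 59, three below the stated requirement. The student total matches neither 74 nor 80 schools. These results rest only on printed figures and simple arithmetic.

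The consequence for power is modest: about 82% against 84% at an effect size of 0.25, assuming two-sided alpha 0.05 and equal allocation. The plan's sample-size statement is wrong and contradictory as written, but on these assumptions 74 schools would not take power below 80% at that effect size.

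**What to change.** Use one number in both sections. The simplest choice is the 80 schools per wave already stated under Participants, with 19,200 students (80 × 240). Show the derivation: 62/0.8 = 77.5, so 78 is the smallest number that meets the requirement and 80 leaves a small margin. Remove 74 and 17,280 from Recruitment; if a minimum is still wanted there, it should be 78 schools (18,720 students).

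Table 1 schedules data collection from 2023 for wave 1 and from 2024 for wave 2, so recruitment may already be complete. If a wave enrolled only 74 schools, keep that number, state that it tolerates 16% attrition (1 − 62/74) and give 17,760 as the student total.

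If at least 78 schools per wave were enrolled, the cost is a change of text alone. The article does not show how many were enrolled.
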